#### Sample size

As no previous studies reported PCOs, we used the incidence of access site complications to estimate the sample size of the SWEET trial. According to previous studies, the incidence of access site complications in percutaneous EVAR was 7.64%, compared with 11.81% in cutdown EVAR (13). We estimated the number of patients needed in this non-inferiority trial with non-inferiority margin of 0.10 (bilateral α 5%, power 80%) by PASS 15.0 software, and 54 patients are required for percutaneous and cutdown EVAR group, respectively. To allow for 10% drop out, 60 patients will be recruited per group, i.e., 120 for Cohort EVAR.

Previous TEVAR studies lacked solid data in above aspects, however, the relevant data of transcatheter aortic valve implantation (TAVI) can be used for reference due to their similar surgical approach (15). The incidence of access site complications was 8.7% in percutaneous TAVI and 8.5% in cutdown TAVI (16). The sample size was calculated with non-inferiority margin of 0.15 (bilateral α 5 %, power 80 %), 45 patients are required for percutaneous and cutdown TEVAR group separately. Fifty patients will be recruited each group allowing for 10% drop out, and the number of subjects in Cohort TEVAR is 100. Therefore, the total sample size of the SWEET trial is 220. The whole calculation process can be found in Supplementary Tables S3, S4 (Supplementary Material).

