**Figure 1 F1:**
[figure not shown]
Flow of participants randomly assigned to percutaneous groups and cutdown groups.

Block randomization stratified by age and body mass index (BMI) using permuted blocks of random sizes will be performed with 1:1 allocation in both cohorts. Randomization sequence is generated by SPSS 26.0 statistical software by a biostatistician. The block size will be concealed until the primary endpoints are analyzed. An independent research coordinator will be responsible for keeping the sequentially numbered allocation sequence list, and will inform the surgeons about the assigned access procedure prior to intervention. To avoid performance bias, every surgeon must have had 10 or more ProGlide procedures, and experience of at least 20 surgical cutdowns to expose the access artery is also needed.

Obviously, trial participants and operating team cannot be blinded to the allocation. The data will be entered into the computer in separate tables by employees outside the research team so that the analysts can analyze data without knowing the allocation information. Therefore, only data analysts are blinded in this study.

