### Statistical methods

#### Analysis population

As Cohort EVAR and Cohort TEVAR were powered and randomized separately, the statistical analysis of both cohorts is planned to be reported separately. The analysis populations of this trial involve modified intention-to-treat (ITT) and per-protocol (PP) populations. The modified ITT is determined after randomization and when the patient started endovascular aortic repair, hence all patients who indeed receive endovascular aortic repair are involved in the primary analysis within the respective access group as originally allocated. In this trial, the modified ITT will be the main analysis set for the summary of both ClinROs and PCOs data. Both ITT and PP analysis are required for test of non-inferiority, and PP analysis serves as a sensitivity analysis. The non-inferiority margin was predetermined at 10%, and the non-inferiority test will be evaluated as a two-sided test at alpha = 0.05. When non-inferiority is reached, ITT is further tested for superiority.

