#### Analysis of primary and secondary outcomes

Generalized linear model (GLM) will be used to compare continuous primary and secondary endpoints, and further adjustment for age, gender, BMI and femoral artery calcification will be performed by multivariate GLM analysis. Logistic regression using generalized estimating equations (GEE) will be applied to compare categorical primary and secondary endpoints. Using multivariate GEE models, the subsequent analysis will be adjusted for age, gender, BMI and femoral artery calcification. The access-related complications are counted and analyzed by the number of femoral accesses instead of the number of patients.

To address heterogeneity among study population, pre-specified subgroup analyses will be performed in the following populations: heavily calcified femoral artery vs. lightly calcified femoral artery, tortuous iliac artery vs. non-tortuous iliac artery, obesity or overweight vs. normal weight, smoking vs. none, elderly or octogenarian vs. younger population.

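### The primary ClinRO is analysed per femoral access but sized per patient, and the 10-point margin has no stated unit; on a per-patient reading it tolerates 10 to about 18 points more EVAR patients with complications

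*Protocol article*

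**What the plan says.** - **Randomisation.** Patients are allocated to an access technique: under Assignment of intervention, "permuted blocks of random sizes will be performed with 1:1 allocation in both cohorts".
- **Sample size, EVAR.** The planning rates are given as "the incidence of access site complications in percutaneous EVAR was 7.64%, compared with 11.81% in cutdown EVAR", with a margin of 0.10. The result is a number of patients: "54 patients are required for percutaneous and cutdown EVAR group, respectively". Dropout is then added: "To allow for 10% drop out, 60 patients will be recruited per group, i.e., 120 for Cohort EVAR". The rates have no stated denominator.
- **Analysis population.** "The non-inferiority margin was predetermined at 10%, and the non-inferiority test will be evaluated as a two-sided test at alpha = 0.05". No unit is given here either.
- **Analysis of primary and secondary outcomes.** "Logistic regression using generalized estimating equations (GEE) will be applied to compare categorical primary and secondary endpoints". The unit for the primary ClinRO follows: "The access-related complications are counted and analyzed by the number of femoral accesses instead of the number of patients".

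The article does not give the number of femoral accesses per patient, and it does not convert the rates, the margin or the size from one unit to the other.

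**The concern.** A risk difference of 10 points per groin and one of 10 points per patient are different criteria wherever some patients have both groins used. A patient with two accesses has two chances of a complication, so a given excess per access is usually a larger excess in patients affected. If the margin was meant per patient, testing it per access loosens the criterion in the direction that favours a claim of non-inferiority. The stated 80% power would also belong to a test other than the one planned.

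GEE with the patient as cluster can give a valid standard error for two correlated groins. It leaves open what the margin means on the patient scale. Because the analysis section fixes the unit explicitly, this is not a detail left open for a later document.

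**Working it through.** **1. Reproduce the planned size.** Inputs from Sample size: control rate pC = 0.1181, percutaneous rate pT = 0.0764, margin 0.10, power 80%. With one binary observation per patient and unpooled variance:

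n per group = (z_α + z_β)² × [pC(1−pC) + pT(1−pT)] / (0.10 + pC − pT)²

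- Variance term: 0.10415 + 0.07056 = 0.17472.
- Distance: 0.10 + 0.0417 = 0.1417; squared, 0.020079.
- One-sided α 0.05: 6.1826 × 0.17472 / 0.020079 = 53.8, so 54. This matches the protocol, and 54 / 0.90 = 60 also matches.
- One-sided α 0.025 (two-sided 0.05): 7.8489 × 0.17472 / 0.020079 = 68.3, so 69. This does not match. Power at 54 per group is then about 70%.

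So 54 is obtained with one observation per randomised patient and no term for accesses or clustering. The gap between one-sided and two-sided α is a separate matter, used here only to restate power.

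**2. Convert between groin and patient.** Assumptions, not in the protocol: 11.81% is a per-patient rate, a share s of patients has two accesses, and the two groins have correlation ρ. With groin rate p:

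P(patient affected) = s × [2p − p² − ρp(1−p)] + (1−s) × p

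Solve for the groin rate that gives 0.1181, add 0.10, and convert back.

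| s | ρ | Control groin rate | Groin rate at margin | Patients affected at margin | Excess over 11.81% |
|---|---|---|---|---|---|
| 1 | 0 | 6.09% | 16.09% | 29.6% | 17.8 points |
| 1 | 0.3 | 7.16% | 17.16% | 27.1% | 15.3 points |
| 1 | 0.5 | 8.09% | 18.09% | 25.5% | 13.7 points |
| 0.5 | 0 | 8.09% | 18.09% | 25.5% | 13.7 points |
| 0.5 | 0.5 | 9.63% | 19.63% | 23.6% | 11.8 points |
| 0 | any | 11.81% | 21.81% | 21.8% | 10.0 points |
| any | 1 | 11.81% | 21.81% | 21.8% | 10.0 points |

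At s = 1 and ρ = 0, a per-patient margin of 10 points corresponds to 11.57% − 6.09% = about 5.5 points per groin.

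**3. Chance of declaring non-inferiority at a true 10-point per-patient excess.** Same per-patient reading, s = 1, 54 patients (108 accesses) per group, Wald risk-difference test at one-sided 0.025. The patient rates 11.81% and 21.81% convert to groin rates gC and gT, with SE = √{[gC(1−gC) + gT(1−gT)](1+ρ)/108} and chance = Φ[(0.10 − (gT − gC))/SE − 1.96].

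- ρ = 0: difference 0.0548, SE 0.0384, chance 21.6%.
- ρ = 0.3: difference 0.0643, SE 0.0470, chance 11.5%.
- ρ = 0.5: difference 0.0723, SE 0.0532, chance 7.5%.
- ρ = 1: difference 0.10, chance 2.5%, the nominal level.

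**4. The other reading: rates and margin per access.** The calculation then needs 54 accesses per group. With two accesses each, 54 patients supply 108, worth 108/(1+ρ) independent ones: 108 at ρ = 0, 72 at 0.5, 54 at 1. On this point the size is never too small. Ten points per access (11.81% to 21.81%) still means, with two accesses in everyone, 38.9% − 22.2% = 16.6 patient points at ρ = 0 and 30.3% − 17.0% = 13.3 at ρ = 0.5.

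**The case against.** The strongest reply is that the protocol never calls the rates or the margin per patient. Only the resulting count is in patients, the supplementary tables with the full calculation are not in view, and the intervention acts on the access site, so a per-access estimand with GEE is legitimate. If the source rates and margin are per access, margin and analysis agree, the test keeps its nominal level against a per-access null, and the error rates in step 3 do not apply. This stands, and it makes the size of the problem conditional. It does not remove the mismatch: the size treats each patient as one observation, the analysis does not, and the reader is not told which unit the margin has.

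Three stronger inferences are tempting and are not supported:

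- **The plan accepts 18 points more patients with complications.** That is the extreme. It needs a per-patient rate, two accesses in every patient and independent groins, none of which is stated. Two groins share a patient and an operation, so independence is no obvious default.
- **Clustering is ignored.** GEE is planned and can handle it.
- **The trial has too few units because accesses were not counted.** On the per-access reading the discrepancy is conservative.

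The step 3 figures also rest on a Wald risk difference, whereas the plan names logistic GEE and does not say how a 10-point margin is applied to it.

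**Conclusion.** The point holds as an unreconciled unit of analysis for the primary ClinRO. The test described in the analysis section is not the one that was sized, and the margin has no unit. On the per-patient reading, 10 points per access in EVAR tolerates a per-patient excess of between 10 and about 18 points, depending on the share of bilateral access and the within-patient correlation. With all patients bilateral, the chance of declaring non-inferiority at a true 10-point per-patient excess is about 22% (correlation 0) to 7.5% (correlation 0.5) instead of 2.5%. On the per-access reading there is no inflation against the stated margin and the size is conservative, but the per-patient consequence of the margin still exceeds 10 points wherever both groins are used and the groins are not perfectly correlated. The documents do not settle which reading applies. That the margin is per patient is an inference from its use in a calculation of patient numbers.

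**What to change.** Define the primary ClinRO per patient, as at least one access-related complication at any femoral access by 1 month (yes/no), and test the margin on the difference in that proportion. Keep the per-access GEE as a supportive analysis, reported with the number of accesses per patient in each arm. State the unit of the planning rates and of the margin. If the sponsor prefers a per-access primary analysis, the margin should be justified on that scale together with what it implies for patients.

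The change needs no new data and little text, and it brings the analysis into line with the unit of randomisation and sizing. It should be made before any unblinded look, including the planned interim analysis. It has a cost: some precision is lost against the per-access analysis, and power must be restated for the per-patient test. At 54 per group that is about 70% with the two-sided 0.05 named in the protocol; 80% holds only at one-sided 0.05, and 80% at two-sided 0.05 needs 69 per group before dropout.

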#### Handing of missing data

Missing data for baseline covariates will be addressed by multiple imputation in overall adjusted analyses, but those patients will not be included in the corresponding subgroup analysis.

### Monitoring

#### Data monitoring

Data Monitoring Committee (DMC), completely independent of the research team, will monitor the validity of data through reviewing interim analysis related to primary outcomes. And the interim analysis would be conducted by an independent statistician after 50% participants have been randomly assigned and completed a 3-month follow-up. The DMC will also make recommendations for the amendments of the study protocol according to the results of interim analysis.

#### Harms

Adverse events are defined as any unfavorable and unintended experience happening to participants during hospitalization and follow-up, whether they are considered to be related to the intervention or not. The presence of underlying disease at enrollment will not be reported as an adverse event, but any increase in the severity of the underlying disease will be considered an adverse event. Details of all adverse events reported voluntarily by participants or observed by investigators will be recorded on the case record forms, such as start date, end date, action taken, results etc.

Any event leading to death, prolonged or renewed hospitalization, disability or permanent damage could be described as a serious adverse event, which should be reported to the ethics committee timely. The principal investigator is required to conduct periodic cumulative reviews of all adverse events and, if necessary, convene meetings to assess the risks and benefits of the study.

#### Auditing

The DMC initial meeting will be held early stage of study, and the agenda contains familiarizing study background, reviewing study protocol, and setting a deadline of interim analysis report etc. Every 6 months, DMC will review enrollment data, adverse events data, validity and completeness of study data with unlimited access. If necessary, the DMC may request additional analysis beyond the interim analysis or an unscheduled security meeting to further understand the efficacy and safety of the trial.

### Ethics considerations and dissemination

#### Ethic approval

Ethics approval has been obtained from the Ethics Committee on Biomedical Research, West China Hospital of Sichuan University (approval number: 2021-1316) on 8th November 2021. Informed consent will be obtained from all participants, and the trial will be conducted in compliance with the Declaration of Helsinki and other regulations.

#### Protocol amendments

The protocol of SWEET trial may be amended during the progress of the trial, and any major amendments will be notified to the accredited medical research ethics committee and competent authority. Any revision in the informed consent forms will also be updated to the patients. Major amendments are defined as any change to the protocol that is likely to affect the conduct or management of the trial, safety of the patients or intervention details. Potential major amendments may include sample size adjustment based on actual clinical outcome difference between two groups, newly added outcomes and adjustment in statistical methods.

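### The protocol permits resizing on the observed group difference, with no stated rule or cap, while the final non-inferiority test stays at an unadjusted 0.05

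*Protocol article*

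**What the plan says.** Four sections of the protocol article bear on this.

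- **Data monitoring.** An independent committee "will monitor the validity of data through reviewing interim analysis related to primary outcomes". On timing, "the interim analysis would be conducted by an independent statistician after 50% participants have been randomly assigned and completed a 3-month follow-up". On consequences, "The DMC will also make recommendations for the amendments of the study protocol according to the results of interim analysis".
- **Protocol amendments.** Changes that count as major go to the ethics committee and the competent authority. The examples given are "sample size adjustment based on actual clinical outcome difference between two groups, newly added outcomes and adjustment in statistical methods".
- **Auditing.** Beyond the planned look, "the DMC may request additional analysis beyond the interim analysis", with no limit on number.
- **Analysis population.** For the final analysis, "the non-inferiority test will be evaluated as a two-sided test at alpha = 0.05". Then: "When non-inferiority is reached, ITT is further tested for superiority".

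The Sample size section sizes both cohorts as fixed designs.

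**The concern.** A sample size set from the difference between the two groups depends on the estimated treatment effect. If the second half is made larger or smaller because of what the first half showed, and the trial is then tested as though its size had been fixed in advance, the final statistic no longer has its nominal distribution under the null. The error at stake is a false claim that percutaneous access is non-inferior to cutdown.

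There is a second route to bias. Participants and operators know the allocation, and one primary outcome, time back to normal life or work, is collected by telephone interview and clinic check. An amendment that resizes the trial from the observed difference tells an open-label team something about that difference.

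**Working it through.** **Inputs.** The final level is two-sided 0.05 (Analysis population), which for non-inferiority means one-sided 0.025 and a critical value of 1.960. The look comes at 50% of participants (Data monitoring); I assume this is half the information in the cohort analysed. No resizing rule is given, so I show a range.

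**Step 1: the plan's own sample size.** With n = (z₁₋α + z₀.₈₀)² × [pT(1−pT) + pC(1−pC)] / [margin − (pT − pC)]²:

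- EVAR (7.64%, 11.81%, margin 0.10): the variance sum is 0.0764×0.9236 + 0.1181×0.8819 = 0.1747 and the distance is 0.10 + 0.0417 = 0.1417. At one-sided 0.05, 6.183 × 0.1747 / 0.1417² = 53.8, so 54.
- TEVAR (8.7%, 8.5%, margin 0.15): the variance sum is 0.1572 and the distance is 0.148. This gives 44.4, so 45.
- Dividing by 0.9 for dropout gives 60 and 50.

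The stated figures are reproduced, as a fixed design with nothing allowed for resizing. They match one-sided 0.05; at one-sided 0.025 the same formula gives 69 and 57. That mismatch is a separate matter. It matters here only because it leaves two candidate baseline levels, so both appear below.

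**Step 2: effect of resizing at a given interim result.** Let x be the half-way z statistic at the edge of the null. Let r be the size of the second stage relative to the first (planned r = 1). The conventional final statistic is (x + √r·Z₂)/√(1+r), so the chance of a false claim given x is

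`1 − Φ[(1.960·√(1+r) − x)/√r]`

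| Interim x | r = 0.1 | r = 1 (planned) | r = 3 |
|---|---|---|---|
| 0 | <0.001 | 0.003 | 0.012 |
| 1 | 0.0004 | 0.038 | 0.046 |
| 2 | 0.430 | 0.220 | 0.134 |

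Enlarging after a weak interim raises the error, as does shrinking after a strong one. Enlarging after a strong interim lowers it.

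**Step 3: overall type I error.** I integrate the Step 2 formula over x ~ N(0,1). Worst case means the most unfavourable r in the allowed range at every x. Conditional power (CP) uses the observed trend, `1 − Φ[(1.960·√(1+r) − x)/√r − x·√r]`.

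| Allowed second stage | Nominal one-sided 2.5% | Nominal one-sided 5% |
|---|---|---|
| r = 1, no change | 2.5% | 5.0% |
| r from 1 to 3, worst case | 3.1% | 6.1% |
| r from 1 to 3, set for 80% CP | 3.0% | 5.9% |
| r of 1 or more, unlimited, worst case | 4.3% | 8.2% |
| r from 0 to 3, worst case | 4.9% | 9.3% |
| Any r, worst case | 6.2% | 11.5% |
| r = 3 only when CP at r = 1 is 20–80% | 2.4% | 4.8% |

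The unrestricted figure has a closed form: 0.025 + exp(−1.960²/2)/4 = 0.025 + 0.1465/4 = 0.0616. A cap of r = 3 doubles the trial, since (1+3)/(1+1) = 2: EVAR 120 to 240, TEVAR 100 to 200.

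**The case against.** The strongest reply is that the amendments section is a notification duty, not an adaptation rule. It gives examples of what may count as major and names neither the interim look nor the monitoring committee. Boundaries and re-estimation rules commonly sit in an analysis plan or committee charter that is not shown. The interim is run by an independent statistician for an independent committee.

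Much of this stands. Missing boundaries are no finding here, and independence limits bias. But the concern rests on written text: sample size may follow the observed difference, the committee recommends amendments from interim results, and the final level is fixed at 0.05. Independence and ethics notification do not control type I error.

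Three stronger readings are tempting, and the document does not support them:

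- *Two unadjusted looks, hence 8.3% two-sided.* That needs a success claim at the look. No section provides for one, so the figure does not apply.
- *The half-way look drives outcomes and statistical methods.* Only sample size is tied to the observed difference. New outcomes and changed methods are listed with no stated trigger, and nothing says a primary outcome or margin may be replaced. The Data monitoring wording merely leaves these changes open to interim results.
- *The interim is declared unblinded.* Data monitoring does not say the outcomes are compared by group, and Assignment of intervention says analysts work without allocation. A by-group look is a reasonable inference, because the difference cannot be used without it.

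Nor is inflation inevitable, as the last row of the table shows.

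**Conclusion.** The point holds as a permission that is too wide, not as a demonstrated error rate. With the conventional final test, resizing on the observed difference can raise one-sided type I error from 2.5% to about 3.1% (second stage capped at three times planned), 4.3% (unlimited increases) or 6.2% (shrinkage also allowed). The first is modest. The last two need the most unfavourable choice at every interim result, so they are bounds, not forecasts. Because the protocol gives no cap, direction or rule, it does not secure the modest case.

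The figures assume a normal statistic, half the information at the look, and no claim at the look. The effect of changing methods after seeing results cannot be calculated. The plan should be amended, but the defect is confined to wording and is cheap to remove.

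**What to change.** - **Protocol amendments.** Allow re-estimation only from the blinded pooled complication rate. If the sponsor wants resizing on the effect, allow it only under a pre-specified rule (trigger, cap, direction) with a combination or conditional-error test at the end.
- **Data monitoring and Auditing.** State that no efficacy or non-inferiority claim will be made from the interim analysis or from any additional analysis the committee requests.
- **Protocol amendments again.** State that primary outcomes, margins and the primary analysis may not change after any between-group comparison, and that outcomes added later are exploratory.

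The cost is wording in three sections and the loss of ad hoc effect-driven resizing. The final alpha stays at 0.05. The effect-based alternative also requires writing the rule and the test in advance.
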